## Abstract

**Background:**

General practitioners (GP) and community pharmacists need information about hospital discharge patients’ medicines to continue their management in the community. This necessitates effective communication, collaboration, and reliable information-sharing. However, such handover is inconsistent, and whilst digital systems are in place to transfer information at transitions of care, these systems are passive and clinicians are not prompted about patients’ transitions. There are also gaps in communication between community pharmacists and GPs. These issues impact patient safety, leading to hospital readmissions and increased healthcare costs.

**Methods:**

A three-phased, multi-method study design is planned to trial a multifaceted intervention to reduce 30-day hospital readmissions. Phase 1 is the co-design of the intervention with stakeholders and end-users; phase 2 is the development of the intervention; phase 3 is a stepped wedge cluster randomised controlled trial with 20 clusters (community pharmacies). Expected intervention components will be a hospital pharmacist navigator, primary care medication management review services, and a digital solution for information sharing. Phase 3 will recruit 10 patients per pharmacy cluster/month to achieve a sample size of 2200 patients powered to detect a 5% absolute reduction in unplanned readmissions from 10% in the control group to 5% in the intervention at 30 days. The randomisation and intervention will occur at the level of the patient’s nominated community pharmacy. Primary analysis will be a comparison of 30-day medication-related hospital readmissions between intervention and control clusters using a mixed effects Poisson regression model with a random effect for cluster (pharmacy) and a fixed effect for each step to account for secular trends.

**Trial registration:**

This trial is registered with the Australian New Zealand Clinical Trials Registry: ACTRN12624000480583p, registered 19 April 2024.

**Supplementary Information:**

The online version contains supplementary material available at 10.1186/s13063-024-08496-w.

## Background

Medication-related harm (MRH) is a significant public health issue, an Australian *National Health Priority*, and the focus of the World Health Organisation’s (WHO) Third Global Patient Safety Challenge [1]. The WHO estimates that medication-related problems cost the economy more than US$42 billion annually, with many of these costs arising during transitions of care [2]. An estimated 250,000 Australian hospital admissions and 400,000 emergency department presentations annually are a direct result of medication-related problems [3]. The post-hospital discharge period is a particularly high-risk period for MRH [4], with a 2018 systematic review showing that 17–51% of older people experience MRH within 30 days of hospital discharge [5]. Furthermore, older people with multiple co-morbidities are at higher risk of readmissions that result from MRH [3, 6–10]. Considering the increase in numbers of older people with multiple co-morbidities and medicines to manage these co-morbidities [7], there is a need to address medicine handover at discharge from hospital to primary care clinicians such as general practitioners (GPs) and community pharmacists. Quality medicine handover necessitates effective communication, collaboration, and reliable information-sharing between the hospital and primary care sectors [5, 11, 12].

Australian standards require hospitals to provide current medicine lists to patients at transitions of care and for the lists to be incorporated into discharge summaries to receiving clinicians [13]. However, studies highlight poor adherence to this activity with inconsistent information transfer from hospitals to GPs and community pharmacists [14–18] and delays in GPs receiving discharge summaries [19, 18]. Ethnographic research identified unclear processes for transferring discharge information and accountability to GPs [20]. GPs may therefore not be informed of patients’ transitions of care journey, relying instead on patients to provide information about their hospital encounters. This lack of communication with GPs contributes to fragmented care and medicine safety risks as delayed, inaccurate, low quality, or incomplete communication from hospitals to GPs contributes to patients’ risk of MRH [11, 12, 21, 22] and hospital readmission [23]. There is also lack of consideration about how patients and families can contribute to enabling effective communication and information-sharing [24, 25].

A 2016 systematic review and meta-analysis showed that pharmacist-led medicine reconciliation programs at hospital discharge are effective in reducing adverse medication-related hospital and emergency department revisits (67% and 28% relative reduction; risk ratio [RR] = 0.33, 95% CI: 0.20–0.53; RR = 0.72, 95% CI: 0.57–0.92 respectively) and all-cause hospital readmissions (19%; RR 0.81, 95% CI: 0.70–0.95) [26]. An Australian randomised trial [27] found that a general practice pharmacist conducting comprehensive medication reviews post-discharge in high-risk patients resulted in a 64% reduction in 30-day, all-cause hospital readmissions and representations (fully adjusted incidence rate ratio = 0.36; 95% CI: 0.15–0.87) [27]. A 2020 systematic review and meta-analysis also showed pharmacist-led interventions with primary care collaboration are effective at reducing readmissions, especially at 30 days follow-up [28]. However, these reductions in hospital admissions are based on a variety of interventions with a need for the standardisation of pharmacist-led medicine reconciliation and transfer of information from hospitals to GPs and community pharmacists.

This brings a need for better integration of digital systems to facilitate medicine information handover at transitions of care [29] and overcoming the current lack of interoperability between software platforms [30, 31] and low uptake and utilisation of digital solutions by clinicians [32, 33]. As a result of these shortcoming, primary care clinicians may not be aware or prompted of patients’ transitions of care or discharge from hospital [32, 33], which is in addition to identified gaps in communication between community pharmacists and GPs [34, 35]. The need for a functional, real-time, secure, and interoperable communication system between GPs and pharmacists is even more important for complex patients with polypharmacy.

## Methods

The proposed study aims to improve medicine handover and digital communication between hospitals, GPs, and community pharmacists when patients are discharged from hospital to primary care. It also aims to increase the uptake of post-discharge medication management reviews by community and credentialed pharmacists. We hypothesise that the co-designed multifaceted intervention will reduce 30-day medication-related hospital readmissions. Secondary outcomes include patients’ understanding of their medicines, quality of life, and health care usage.

Consumer involvement in the study will be aligned with the Guidance for Reporting Involvement of Patients and the Public (GRIPP2) checklist [36]. We followed the SPIRIT criteria [37] in the development of the trial. The stepped wedge cluster randomised controlled trial (SW-CRT) will comply with the extension of the CONSORT 2010 Statement for stepped wedge cluster RCTs [38].

### Study design and setting

A three-phased, multi-method study design will be followed that is underpinned by the Knowledge-to-Action Framework [39, 40]. Ethics approval for phases 1 and 2 was obtained from the Gold Coast Hospital and Health Service (GCHHS) Human Research Ethics Committee on 16 October 2023 (HREC/2023/QGC/101063, [contact]). The phase 3 trial was registered with the Australian New Zealand Clinical Trials Registry on 19/04/2024: ACTRN12624000480583p; ethics approval is pending. All items of the World Health Organization Trial Registration Data set are covered in the manuscript.

The multifaceted intervention will involve structured discharge medicine handover from hospitals to community pharmacies where clustering will occur. The community pharmacies are located within the geographical areas serviced by two hospital and health services in South-East Queensland, Australia, namely GCHHS and Metro South Hospital and Health Service (MSHHS), incorporating a mixture of seven tertiary, secondary, and regional hospitals. All study hospitals are part of Queensland Health, the public health service in the state of Queensland, Australia. Queensland Health incorporates 16 hospital and health services. All participating hospitals use a Cerner® electronic medical record system, referred to as the integrated electronic Medical Record (ieMR) system.

We hypothesise our multifaceted intervention will reduce 30-day hospital readmissions due to medication related complications. In addition, we expect our intervention will increase medicine information handover between hospital, GPs, and community pharmacists; increase the uptake of post-discharge medication management review services and medicine reconciliation by community and accredited pharmacists; improve medicine information communication between primary care clinicians; increase patients’ self-reported quality of life and understanding of their medicines and how to take them; and reduce health care usage (regardless of cause).

#### Phase 1: Co-design of intervention with stakeholders and end-users over 9-month period

Key learnings from previous studies [18, 27, 30, 31, 41, 42] and workshops will be used to co-design and integrate the perspectives of hospital and primary care clinicians (GPs, community and credentialed pharmacists), consumers, and other relevant stakeholders. There will be 8–10 1-h co-design workshops with hospital and primary care clinicians, three 2-h workshops with healthcare consumers, and one workshop combining clinicians and consumers. Workshops will be facilitated by two experienced team members (LH and LO), and participants will be invited to share ideas on potential solutions to enhance medicine handover during transfer from hospital, including suggestions on a potential digital solution.

#### Phase 2: Development of the intervention over 12-month period

Building on the results of the phase 1 workshops, this phase will develop infrastructure and resources to streamline medicine information handover from hospital to the community setting. This phase involves four key steps to ensure success: developing handover guidelines, developing and pilot testing a digital solution, customising the intervention, and defining the clusters for the phase 3 trial.

We have partnered with the Pharmaceutical Society of Australia (PSA, the peak Australian pharmacist professional organisation), established software vendors, key stakeholders (hospital and primary care clinicians, managers and department heads), and healthcare consumers to identify, modify, or develop a digital solution based on the user requirements identified in the co-design phase. The digital solution will be pilot tested and refined with end-users: around five general practices and five community pharmacies and one of the participating hospitals [43]. Scenario-based usability testing followed by a debrief interview will allow for qualitative feedback to determine intervention usability and acceptability. In concert, we will collaborate with healthcare consumers and the PSA to develop guidelines and training modules to upskill community pharmacy staff in transitions of care, including the new digital solution.

Retrospective hospital data will be used to identify postcodes within the catchment areas of the two hospital and health services that contain populations of community dwelling patients who have a high prevalence of hospital readmission within 30 days after discharge from a previous admission. These data will be used to identify clusters of community pharmacies that are located within these ‘high-risk’ (of readmission) populations.

#### Phase 3: Stepped wedge cluster randomised controlled trial (SW-CRT) of newly designed intervention over 12-month period

We will perform a 12-month SW-RCT [44], comparing the intervention with standard care. Twenty clusters of community pharmacies will be pragmatically allocated to receive the intervention. Data will be collected from all clusters over the study period. Each cluster will provide before and after intervention data. This study design is represented in Fig. 1. The anticipated date of first enrolment is 1 October 2025, and last day for recruitment is 30 September 2026.

**Fig. 1 Fig1:**
[figure not shown]
Multifaceted intervention

A hospital *pharmacist navigator* will facilitate a medicine handover at each of the participating hospitals. Navigators will work with the patient to connect with their nominated community pharmacy and GP. Using established medication management review *(MMR) services*, the patient’s medicines will be reconciled at the primary care level in the community pharmacy or in the patient’s home and follow-up actions communicated to the GP (Fig. 2). An innovative *digital solution* (Fig. 3) will link hospitals, community pharmacists, GPs, and patients together and, through asynchronous communication, provide all parties with information on all actions being performed throughout the transition of care.

**Fig. 2 Fig2:**
[figure not shown]
Provision of medication management review services

**Fig. 3 Fig3:**
[figure not shown]
Digital solution

The SW-CRT design will be used to assess the effects of the multifaceted intervention over a 30-day follow-up period following hospital discharge. A 1-month lead in phase is included, where the pharmacy cluster is not considered as being in either the control or intervention phase, and the data collected during this time will not contribute to the final outcome analysis. The SW-CRT design will enable the intervention to be provided at every community pharmacy cluster by the end of the study period, to measure possible underlying temporal trends (such as seasonal variation in admissions) and to prevent potential direct/indirect educational effects of the intervention carrying over to the control phase (which precludes a crossover design). Phase 3 will incorporate an evaluation of the impact of the intervention on key outcomes, a process evaluation, and an economic evaluation.

### Phase 3 sample size

The phase 3 sample size was calculated for the primary outcome, taking into account the intracluster correlation coefficient (ICC), the expected baseline number of readmissions, effect of the intervention, and the desired power of the study (power = 80%, *α* = 0.05) [44, 45]. Patterns of ICCs were drawn from other sources [27, 46] to assume an ICC of 0.15. Based on previous studies [27, 28], it is estimated there will be a reduction in unplanned readmissions from 10% in the control group to 5% in the intervention at 30 days. With an expected 20% drop out rate and aiming for 90% power, we aim to recruit 10 patients per pharmacy cluster per month which will provide a total sample size of 2200 (excluding the cluster lead-in period).

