### Study outcomes

#### Primary outcome

The primary outcome for the study is a comparison between intervention and control patients of (mean and median) unplanned hospital readmissions at 30-days post-discharge due to medicine-related harm as defined and ascertained below.

Hospital readmission events will be collected from the electronic medical record systems of the seven trial hospitals. The indexed admission will be any inpatient admission via any pathway (e.g. emergency department, elective surgery, outpatients) with an unscheduled representation to the emergency department within 30 days of discharge from the indexed admission. A panel consisting of four senior clinicians (emergency physician, geriatrician, specialist in general medicine, pharmacist) will consider each readmission event to determine if it is possibly medication related and assess its causality, severity, and preventability as MRH [48–50]. The panel will be blinded as to whether the readmission event came from an intervention or control cluster. Each event will be recorded by considering:What was the medicine?What was the event?Has the participant experienced MRH (doubtful, possible, probable or definite) [49]?

MRH will be defined as harm from non-adherence to a prescribed medicine, unintentional medicine error, or adverse medicine reaction [5, 51] within 30 days post-discharge from hospital. It will exclude intentional overdose or misuse but will include unintentional overdoses or misuse. Where the patient is considered to have experienced MRH (definite, probably and possible), the panel will further consider:Was the MRH preventable (definite preventable, possibly preventable, not preventable or unable to evaluate) [48, 49]?What was the severity (fatal, life-threatening, serious or significant) [50, 52]?What was the main cause (adverse drug reaction, unintentional error, non-adherence) [52]?

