### Data analysis

Phase 1 and 2 qualitative data will be thematically analysed [57, 58]. Audio recordings will be professionally transcribed verbatim by an independent party and the transcripts quality screened and cross-referenced. The NVivo© software (QSR International Pty Ltd, Chadstone, Australia) will be used for coding by two coders. Where there are differing interpretations, the differences will be discussed between the members of the research team until consensus is reached. Data will be thematically analysed to identify underlying themes.

All phase 3 participants (excluding those recruited in the lead-in phase) will be included in the analysis. Each cluster will be classified as being in the intervention or the control phase based on their pre-specified randomised crossover time, regardless of whether crossover is achieved at that time. In the primary analysis, overall differences in readmissions will be modelled using a mixed effects Poisson regression model with a random effect for cluster (pharmacy) and a fixed effect for each step to account for any secular trend. Secular trends may include seasonal variation in readmissions or changes in practice (outside of the project’s control). We also intend to allow for both levels of clustering at the analysis stage, i.e. we will allow for both clustering by hospital and clustering by pharmacy (the unit of randomisation). This will be achieved by including both a random effect for community pharmacy hub and a random effect for hospital. Robust standard errors will be used to allow for the misspecification of the error structure when using the Poisson model to model binary events. We will report treatment effects both on the relative and absolute scale. We will also report estimates of intra cluster correlations. Secondary analysis will be conducted using similar techniques. The primary and secondary outcomes will be considered significant at the 5% level, and 95% confidence intervals will be reported. Missing outcome data is likely to be minimal for this study as it is routinely collected through hospital records. If the level of missing patient characteristic data is above 5%, we will use multiple imputation methods which allow for clustering and time effects. We will not conduct an interim analysis.

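### The sample size uses rates for unplanned readmissions (10% to 5%), but the primary outcome is the narrower medication-related readmission, for which no rate, effect or power is stated

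*Protocol article*

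**What the plan says.** Phase 3 sample size states that the calculation was done for the primary outcome. The event it uses is unplanned readmission: "it is estimated there will be a reduction in unplanned readmissions from 10% in the control group to 5% in the intervention" at 30 days, based on two cited sources. The Methods paragraph of the Abstract repeats the same rates and the same label.

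The Primary outcome section defines something narrower: "unplanned hospital readmissions at 30-days post-discharge due to medicine-related harm". A blinded four-person panel reviews each readmission event and judges whether it was medication-related. The Abstract agrees: "Primary analysis will be a comparison of 30-day medication-related hospital readmissions between intervention and control clusters". The hypotheses in the opening of Methods and in Study design and setting also concern medication-related readmission.

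The Background describes the two sources behind the rates. One is a trial reporting a 64% reduction in all-cause readmissions and representations. The other is a meta-analysis reporting on readmissions. Neither is described as medication-related.

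Phase 3 sample size gives two power levels: "the desired power of the study (power = 80"%, and later "With an expected 20% drop out rate and aiming for 90% power".

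**The concern.** The sizing and the primary test name different events. Panel-confirmed medication-related readmissions are picked out of the unplanned readmissions. If 10% is the rate of all unplanned readmissions, the medication-related rate cannot exceed 10%, and it reaches 10% only if the panel attributes every event to medicines. For a fixed relative effect, a lower control rate means lower power.

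Without a stated rate for the primary outcome, a reader cannot tell what the trial can detect. A null primary result would be read against a power figure that belongs to another endpoint. No interim analysis is planned that could reveal the difference.

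**Working it through.** **Inputs from the article.** 20 clusters, 12 months, 10 patients per cluster-month, one lead-in month per cluster left out of the analysis, ICC 0.15, 20% drop-out, and a fixed effect for each step. The 5% level comes from Data analysis ("The primary and secondary outcomes will be considered significant at the 5% level"). A two-sided test is assumed because "95% confidence intervals will be reported".

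**Assumed.** The number of steps is not in the text and the design figure is not shown. I take 10 sequences of 2 clusters, crossing one month apart.

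**Headcount.** 20 × 10 × (12 − 1) = 2200, as stated.

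**The plan's own rates, 10% to 5%.** Two individually randomised groups at 80% power need 435 each, 870 in all. The Woertman design effect with 10 steps, one baseline month and 10 per month is

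(1 + 0.15 × 109)/(1 + 0.15 × 59) × 3 × 0.85/(2 × 9.9) = 0.227.

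870 × 0.227 gives 197 per month, and over 11 months 2171. So 2200 fits 80% power with no drop-out and no lead-in gap. At 90% power the same method needs about 2905, or 3631 after allowing for drop-out.

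**Model with the lead-in month removed (Hussey-Hughes).** For mean proportion p̄, σ² = p̄(1 − p̄). The covariance of a cluster's monthly means is V = [σ²(1 − ICC)/m]·I + ICC·σ²·J, with month fixed effects and a treatment term. The variance of the treatment effect is the last diagonal element of (ΣX′V⁻¹X)⁻¹. For this layout it equals 0.00556σ² with m = 10 and 0.00689σ² with m = 8 (20% of outcomes lost). Then

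z = |p₀ − p₁|/√variance, and power = Φ(z − 1.96).

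| Control → intervention | σ² | z, m = 10 | Power | z, m = 8 | Power |
|---|---|---|---|---|---|
| 10% → 5% (stated) | 0.0694 | 2.546 | 72% | 2.287 | 63% |
| 7% → 3.5% | 0.0497 | 2.104 | 56% | 1.891 | 47% |
| 5% → 2.5% | 0.0361 | 1.765 | 42% | 1.586 | 35% |
| 3% → 1.5% | 0.0220 | 1.356 | 27% | 1.219 | 23% |
| 2% → 1% | 0.0148 | 1.103 | 20% | 0.991 | 17% |
| 5% × RR 0.33 = 1.65% | 0.0321 | 2.506 | 71% | 2.251 | 61–62% |
| 7% × RR 0.33 = 2.31% | 0.0444 | 2.985 | 85% | 2.682 | 76–77% |

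Every control rate below 10% is an assumption; the article gives none for medication-related readmission. RR 0.33 is the Background's figure for medication-related hospital revisits. Averaging the two phases' variances instead of pooling them moves any entry by no more than about one point, hence the small ranges in the last two rows.

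**Sensitivity.** With ICC 0.01 and m = 10, 10% to 5% has 78% power and 5% to 2.5% has 47%. Without the lead-in gap (11 months), 10% to 5% has 80% with m = 10 and 72% with m = 8.

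**The case against.** The strongest defence is that the 10% is a loosely labelled figure for the medication-related outcome. The article says the size was calculated for the primary outcome and never writes that the sized event is of any cause. Patients are triaged for risk of medication-related readmission, clusters come from areas with high readmission, and events judged only possibly medication-related appear to count. The medication-related share could therefore be high. This stands as far as it goes: the text does not fix how far below 10% the rate lies, and a reader who infers that the primary event is much rarer goes beyond it. But the label still disagrees with the endpoint, and neither cited source is described as medication-related.

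A reader might also infer that a halving conflicts with the article's own evidence, because one meta-analysis reports "all-cause hospital readmissions (19%; RR 0.81". That does not hold. The sizing cites other sources, and the trial among them found a 64% all-cause reduction. From 10% to 3.6%, the same model gives 93% power (87% with 20% loss).

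The size of the loss depends on the effect. With RR 0.33 from 5%, power is about the same as for the stated 10% to 5%. Data analysis also expects little missing outcome data, so the second figure in each pair is a cautious case.

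**Conclusion.** The point holds as a mismatch between the sizing and the primary endpoint. The stated 80% or 90% power is not established for the primary test, because no control rate or effect is given for medication-related readmission.

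Part of the shortfall is not due to the endpoint. Under the model above, the stated 10% to 5% already gives only 72% (63% with 20% loss). Any lower control rate with the same halving gives less. If the effect is as large as RR 0.33, 80% power needs a medication-related control rate of about 6.1% (7.5% with loss), and 90% needs about 8.1% (9.8%).

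A reader might conclude that a true halving would more likely than not be missed. With full outcome data, that is so at the assumed rates of 5% and below but not at 7% (56%), and the documents do not say which applies. The figures rest on the assumed step layout, a two-sided test and the stated ICC.

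**What to change.** In the Abstract and in Phase 3 sample size, name the endpoint to which the 10% to 5% and the power figure belong. State the expected control-phase rate of medication-related readmission and the expected effect, either as a range or informed by the retrospective hospital data already planned for phase 2. Then restate the power, or the smallest detectable risk ratio, for that endpoint with 20 clusters and 2200 patients. Give one power level, and say whether it allows for drop-out and the lead-in month.

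If a fall from 10% to 5% in all unplanned readmissions is the intended primary endpoint, change the Abstract, the hypotheses in Methods and in Study design and setting, the Primary outcome section and Data analysis to say so. Reporting all unplanned readmissions as a secondary outcome is optional and does not by itself cure the mismatch.

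The cost is a recalculation and some wording. The drawback is that the stated power will probably look less favourable.

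### The sample size paragraph states both 80% and 90% power for one design; 2,200 patients match about 80% at best, with no drop-out allowance

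*Protocol article*

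**What the plan says.** The protocol article, Phase 3 sample size, says the size was calculated for the primary outcome from the ICC, the baseline rate, the effect and "the desired power of the study (power = 80"%, with α = 0.05. It assumes an ICC of 0.15 and a fall in unplanned readmissions from 10% to 5%. The same paragraph then sets recruitment on another basis: "With an expected 20% drop out rate and aiming for 90% power, we aim to recruit 10 patients per pharmacy cluster per month". The total is 2,200, excluding the lead-in period.

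The Phase 3 description gives 20 clusters over 12 months. The text below Figure 3 adds a one-month lead-in whose data are not analysed. The Abstract repeats the size, "to achieve a sample size of 2200 patients powered to detect a 5% absolute reduction in unplanned readmissions", without a power figure. Data analysis specifies a random cluster effect and fixed step effects, and adds: "Missing outcome data is likely to be minimal for this study as it is routinely collected through hospital records".

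**The concern.** One design under one set of inputs cannot have both 80% and 90% power. The text does not present 80% as a minimum, or 90% as the result of a second scenario. Nor does it show how the 20% drop-out enters the total, since 2,200 is simply clusters × months × monthly recruitment.

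Power for the primary outcome is a core design property. A reader who takes the later figure would put the chance of missing a true fall from 10% to 5% at one in ten. If the design supports about 80% at best, that chance is about one in five or more, and a null result would be given more weight than it can bear.

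**Working it through.** **Inputs from the protocol article.** Rates 10% and 5%; ICC 0.15; 20 clusters; 10 patients per cluster-month; 12 months with one excluded as lead-in; random cluster effect and fixed period effects.

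**Assumptions.** The test is two-sided, because the 5% level is paired with 95% confidence intervals ("considered significant at the 5% level, and 95% confidence intervals will be reported"). The number of steps is not in the text and Figure 1 was not available, so 4 to 10 steps are used, with switches spread over the period.

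**1. The stated total.** 20 × 10 × 11 = 2,200. This is the number recruited, before any drop-out.

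**2. Individually randomised size.** Per arm, n = [1.96√(2 × 0.075 × 0.925) + z√(0.10 × 0.90 + 0.05 × 0.95)]² / 0.05². This gives 435 per arm (870 in total) at 80% power and 582 (1,164) at 90%.

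**3. Stepped-wedge design effect (Woertman).** With k steps, t periods per step, b baseline periods and n patients per cluster-period:

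DE = [1 + ρ(ktn + bn − 1)] / [1 + ρ(ktn/2 + bn − 1)] × 3(1 − ρ) / [2t(k − 1/k)]; clusters = N × DE / n.

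For k = 10, t = b = 1, n = 10, ρ = 0.15: DE = 17.35/9.85 × 0.1288 = 0.2268. For n = 8 (20% lost): DE = 14.05/8.05 × 0.1288 = 0.2248.

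| Clusters needed | 80% power | 90% power |
|---|---|---|
| No drop-out (n = 10) | 870 × 0.2268/10 = 19.7 | 1,164 × 0.2268/10 = 26.4 |
| 20% lost (n = 8) | 870 × 0.2248/8 = 24.4 | 1,164 × 0.2248/8 = 32.7 |

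Twenty clusters, and so 2,200 patients, is the answer for 80% power with no drop-out.

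**4. Power of the stated design (Hussey-Hughes variance).** Total variance is (0.09 + 0.0475)/2 = 0.06875, with a random cluster effect and fixed month effects. Power = Φ(0.05/SE − 1.96).

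| Layout | 2,200 analysed | 1,760 analysed |
|---|---|---|
| Complete 11-period wedge, 10 steps | 80.8% | 72.0% |
| Complete 11-period wedge, 4 or 5 steps | 79 to 80% | about 71% |
| Lead-in month removed at each switch, 10 steps | 72.5% | 63.2% |
| Lead-in month removed at each switch, 4 or 5 steps | about 74% | about 65% |

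Both types of layout have 20 × 11 = 220 analysed cluster-months, so 2,200 already excludes the lead-in in each. What differs is where the excluded month falls. At the switch it takes out the months that carry much of the within-cluster information.

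**5. Detectable difference at 80% power, 10 steps (2.80 × SE).** Complete wedge: SE 1.77 points, so 4.9 to 5.0 points with 2,200. Lead-in at each switch: SE 1.96 points, so 5.5 points with 2,200; SE 2.18 points, so 6.1 points with 1,760.

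**The case against.** The first target holds: 80% power, ICC 0.15 and 10% vs 5% lead to 20 clusters and 2,200 patients under a standard formula. A reader might infer that the whole calculation is wrong. It is not: the part that fails is the clause adding 90% power and 20% drop-out. The Abstract adds no contradiction, as it gives no power figure.

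A reader might also take 63 to 72% as the trial's power. That holds only if drop-outs lose the primary outcome. Outcomes come from hospital records and little is expected to be missing, so the loss may be close to nil and power about 72.5 to 81%.

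A third inference is that no smaller ICC would help. Power is not monotone in the ICC: it is lowest near 0.05 to 0.10 and reaches about 82 to 91% at 0.005, depending on layout. But the plan assumes 0.15, and its stated power has to follow from that.

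Finally, the step count and the timing of the lead-in are assumed here, and Figure 1 may show both. This objection stands as a limit on the exact figures. It does not rescue 90%: no layout examined with 4 to 10 steps exceeds 81% at the plan's ICC with a two-sided test. A one-sided 5% test with a common lead-in month gives 88% before drop-out and 82% after, still short.

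**Conclusion.** Wrong as written. The contradiction between the two targets is plain on the page and needs no modelling. The arithmetic shows that 2,200 carries neither the 90% power nor the drop-out allowance. With all 2,200 analysed, power is about 80% at best, or about 72.5 to 74% if the lead-in month falls at each cluster's switch. If the stated 20% drop-out reaches the primary outcome, it is about 63 to 72%.

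These figures rest on a two-sided 5% test, ICC 0.15 constant over time, total variance averaged over the two rates, and 4 to 10 evenly spread steps. The drop-out allowance and the expectation of minimal missing outcome data pull in opposite directions, and the document does not say which governs the analysed number.

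**What to change.** In Phase 3 sample size, delete the 90% clause and keep one power target. Repeat the calculation on the actual step layout, with the lead-in month excluded where it really falls and with the number of patients expected to be analysed. Report the achieved power from that calculation (expected to be about 73 to 81% without outcome loss) or the matching detectable difference. The ranges here should not be copied in place of it.

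Reconcile the 20% drop-out with Data analysis: say what drop-out means in this trial and whether it removes the record-based primary outcome. If it does not, the allowance should cover only those whose records can no longer be used, such as consent withdrawals.

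The cost is a recalculation and a few sentences. The downside is that the stated power becomes less favourable.
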